### Cost-effectiveness analysis

The aim of the economic evaluation is to relate the difference in societal and healthcare costs between the intervention and the control condition to the difference in effect on the outcome measures. Both a cost-effectiveness and cost-utility analysis will be performed with a time horizon of 6 months.

#### Cost analysis

Healthcare costs include costs of primary and secondary care, complementary care, and home care. Other costs include costs of informal care, meal services, and transportation services. Societal costs comprise of both healthcare and other costs. For the valuation of the health care utilization, standard prices published in the Dutch costing guidelines will be used (Hakkaart-van Roijen, Van der Linden et al. [18]). Medication use will be valued according to prices of the Royal Dutch Society for Pharmacy (Z-index. G-Standaard. The Hague, The Netherlands: Z-Index, 2002). Lost productivity of the caregiver will be assessed using the Productivity and Disease Questionnaire (PRODISQ; Koopmanschap (Koopmanschap [23]). The friction cost approach will be used to estimate lost productivity costs.

#### Patient outcome analysis

Societal costs will be related to the following effect measures in the economic evaluation:

(i) quality-adjusted life-years (QALYs) based on the Dutch tariff for the EuroQol (EQ-5D-5L; Group [17]) at the level of the caregiver; (ii) quality of life of the person with dementia using the Dementia Quality of Life scale (DQoL). The analysis will be performed according to the intention-to-treat principle. Missing cost and effect data will be imputed using multiple imputation. Incremental cost-effectiveness ratios (ICERs) will be calculated by dividing the difference in mean total costs between the treatment groups by the difference in mean effects. Bootstrapping with 5000 replications will be used to estimate the 95% confidence intervals around cost differences and the uncertainty surrounding the ICERs. Uncertainty surrounding the ICERs will be graphically presented on cost-effectiveness planes. Cost-effectiveness acceptability curves showing the probability that the intervention is cost-effective in comparison with usual care for a range of different ceiling ratios will also be estimated.

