Caring for people with dementia living at home is challenging, which is why home-based psychosocial interventions are highly needed to reduce caregiver burden. There is preliminary evidence to support the acceptability of psychosocial interventions for dementia caregivers (Qiu, Hu et al. [35]). For example, it has been found that peer support can significantly improve well-being of caregivers by decreasing feelings of isolation, encouraging better coping strategies, and enabling a change in caregiving behaviour (Brodaty and Donkin [4]), Charlesworth, Burnell et al. [5], (Organization [31]), Sousa, Sequeira et al. [40]). Generally, caregivers often lack social contact and support and experience feelings of social isolation (Brodaty and Donkin [4]), Szcześniak, Rymaszewska et al.[43]), because they lack personal time and opportunities to socialise, and also experience stigma resulting in family and friends distancing themselves (Charlesworth, Burnell et al. [5], Dröes, Meiland et al. [12]). Interventions can offer support to caregivers of people with dementia and can reduce the pressure and distress for the caregiver, which can be of benefit to both the caregiver as well as the person with dementia. Moreover, if nursing home admission of the person with dementia can be postponed (Moon and Adams [27]), the pressure on health and social care services can be reduced (Stall, Kim et al. [42]). Additionally, the costs for long-term residential care of people with dementia could also be reduced, which is important because these are especially high in the Netherlands, and even among the highest in the European Union (Wimo, Jönsson et al. [56]). However, to date there are few effective interventions for caregivers of people with dementia that are widely available. In a review by Sousa et al. (Sousa [41])it was found that the main characteristics of interventions that successfully addressed caregivers’ needs were: (i) six weekly sessions with an average duration of 100 min,(ii) preferred topics ranged from learning and training skills in physical and mental health issues to knowing where to find and how to use available health services; and (iii) greater family and peer support. Based on interviews with caregivers of persons with dementia in different stages of the disease, Boots et al. (Boots [2]) recommended that therapeutic interventions should not be problem-oriented, but instead (i) try to identify the needs of the caregivers’ individual situation, (ii) focus on adaptation rather than on loss, and (iii) increase their knowledge of the disease and future changing roles to reduce the negative consequences of caregiving later on. In turn, caregivers found that the available information on dementia was negative and stigmatizing, and caregivers of persons in more advanced stages of dementia thought that disease-specific knowledge was crucial to help them understand the person with dementia, and improved their ability to empathize with their loved one (Boots, Wolfs et al. [2]).

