A major strength of the current study is that the MOMANT program will take place at local health care organizations in such a way that staff costs and demand on health care services are reduced by training the informal caregiver to provide part of the intervention, and by working with an implementation manual. If study outcomes confirm the effectiveness of the implementation of this intervention, the MOMANT caregiver support program can be further implemented in real-world practices and routine care pathways, thus increasing the number of effectively supported informal caregivers. A second strength of this study is that the intervention includes activities for the caregivers and persons with dementia to do together in order for the person with dementia to be able to participate again in day-to-day life. Additionally, the fact that participants are included across different parts of the Netherlands ensures diversity in the group such that contextual differences can also be assessed. However, letting informal caregivers present part of the intervention could also be considered a limitation in terms of intervention fidelity, resulting in less visibility in the actual practice of how the intervention is presented. Moreover, because of the cluster randomisation there could be a risk of between-group differences at baseline, as well as only recruiting people with dementia who already receive professional (day)care. Despite these limitations, evaluating the effectiveness of this intervention will be a starting point in offering more support to this group of people in the routine care pathways, and therefore also be beneficial for those who do not yet receive professional care.

Effective psychosocial interventions for community-dwelling people with dementia and their caregivers are of the utmost relevance because the number of people suffering from dementia will continue to rise in the years to come, and the large majority lives and are cared for at home by informal caregivers. This study will not only contribute to the knowledge on the effectiveness of a multicomponent training and support intervention, but also on its implementation in regular care. Through this intervention, we hope to empower both the caregiver and the person with dementia to live a good life with dementia and to become more capable in dealing with future challenges.

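### The ICER is defined without baseline adjustment, and the societal cost definition does not name the cost of delivering the programme

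*Protocol article*

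**What the plan says.** Under Patient outcome analysis, the Protocol article relates societal costs to caregiver QALYs (EQ-5D-5L, Dutch tariff) and to the DQOL of the person with dementia. The ICER is obtained by "dividing the difference in mean total costs between the treatment groups by the difference in mean effects". Missing data are multiply imputed, and 5000 bootstrap replications give the uncertainty. The section mentions no baseline covariate and no regression model.

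Two other sections bear on this. Data management / statistical analysis says that analyses will be adjusted for baseline scores and confounders by entering them in the regression models. The Discussion concedes that "because of the cluster randomisation there could be a risk of between-group differences at baseline".

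Under Cost analysis, the first category is set out as follows: "Healthcare costs include costs of primary and secondary care, complementary care, and home care". A second category, called other costs, covers unpaid care by the caregiver, meals and transport. The total is then defined from these two categories: "Societal costs comprise of both healthcare and other costs".

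The same section gives a price source for medication. It also says that "Lost productivity of the caregiver will be assessed using the Productivity and Disease Questionnaire" and, on valuation, that "The friction cost approach will be used to estimate lost productivity costs". The cost of delivering the programme is not named anywhere in the section.

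**The concern.** Cost-effectiveness is part of the main aim, so the definition of the ICER matters as much as the effect model. Two features of the text would distort the ICER if it were followed as written.

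First, a QALY calculated as an area under the utility curve includes the baseline value. If the arms start at different utilities, part of the QALY difference exists before anyone is treated, and a further part persists through the correlation between baseline and follow-up. The article recognises this threat and deals with it in the effectiveness analysis, but the ICER formula has no corresponding step. Multiple imputation and the bootstrap do not re-centre an estimate for an imbalance that has actually occurred.

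Second, delivery takes staff time in one arm only: group sessions led by a professional, a home visit to each dyad, training of the trainers, and manuals. The article presents low staff cost as a strength of the programme, so this item in particular should be counted visibly.

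**Working it through.** **The plan's own figures.** The economic section gives no cost, QALY or ICER to reproduce. The planned effect used as a yardstick below comes from Sample size: d = 0.5, 80% power, alpha 0.05. A two-sample t-test needs 63.8, so 64 per group (power 0.801), as stated. Dividing 64 by 0.75 gives 85.3, in line with the stated 85 recruited per group.

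**QALY weights.** EQ-5D is measured at 0, 3 and 6 months over a 6-month horizon. Assuming the trapezoid rule,

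QALY = 0.125·u0 + 0.25·u3 + 0.125·u6.

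The weights sum to 0.5 year, and baseline utility carries a quarter of that.

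**Effect of an imbalance.** Let D be the baseline utility difference and rho the slope of follow-up on baseline utility. The unadjusted QALY difference then shifts by D × (0.125 + 0.375·rho). With rho assumed to be 0.5 to 0.7:

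| D (assumed) | rho 0.5 | rho 0.7 |
|---|---|---|
| 0.02 | 0.0063 | 0.0077 |
| 0.03 | 0.0094 | 0.0116 |
| 0.05 | 0.0156 | 0.0194 |

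**Is D = 0.03 plausible?** The chance standard error of the baseline difference is SD × √[(2/85) × (1 + (m − 1)·ICC)]. With an assumed utility SD of 0.15 to 0.20:

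- Without clustering it is 0.023 to 0.031.
- With 6 to 8 dyads per centre and an ICC of 0.05 to 0.10 (both assumed) it is 0.026 to 0.040.

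An imbalance of 0.03 is therefore about one standard error.

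**Yardstick.** An effect of d = 0.5 held at both follow-ups gives 0.5 × SD × 0.375, which is 0.028 QALY at SD 0.15 and 0.0375 at SD 0.20. For D = 0.03 the shift is from 0.0094/0.0375 = 25% to 0.0116/0.0281 = 41% of this gain.

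**Delivery time per intervention dyad.** From Intervention: 6 sessions of about 1 h, groups of 4 to 8, one home visit, and trainer training of 2 to 2.5 h. The visit length is not given, so 1 to 2 h is assumed. Each trainer's training is assumed to be spread over one group.

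- Low: 6/8 + 2/8 + 1 = 2.0 h.
- High: 6/4 + 2.5/4 + 2 = 4.1 h.

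At an assumed EUR 40 to 80 per hour, this is 2.0 × 40 = EUR 80 to 4.125 × 80 = EUR 330, against zero in the control arm. Manuals, travel, preparation and the research team's own time are not included. Set against the yardstick gain, the omission would be worth 80/0.0375 = about EUR 2,100 to 330/0.0281 = about EUR 11,700 per QALY.

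**The case against.** The ICER sentence is the generic definition and does not say how the two mean differences are estimated, so adjusted differences would satisfy it. The general statement on baseline adjustment in the statistical section could be read as covering the economic analysis. Both cost lists are introduced as open, the items of the adapted RUD are not shown, and an article may leave costing detail to a fuller document.

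Much of this stands. It shows that the text permits the better analysis, so the point is not that a wrong analysis has been firmly chosen. But the stated adjustment works through regression models, and the economic section has none and does not refer back to them. Likewise, open lists do not settle whether a cost unique to one arm is counted when the societal total is defined as the sum of two categories that do not name it.

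Four stronger inferences are tempting, and the article does not support them:

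- *Lost productivity and medication are left out.* Productivity has both an instrument and a valuation method, and medication has a price source. Only their place in the societal total is unstated.
- *Residential care is left out.* It is not named, although the Background argues that "the costs for long-term residential care of people with dementia could also be reduced". However, the RUD items are unseen and time of admission is recorded. All persons with dementia live at home at entry, so within a 6-month horizon much of any saving may fall too late to count.
- *Medication will be priced at 2002 levels.* The year stands only inside a source reference. The article does not say that prices of that year will be applied.
- *The ICER is biased toward the intervention overall.* Leaving out delivery cost would favour it. Leaving out residential care would work against it if admission is delayed. Chance imbalance can go either way.

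**Conclusion.** The point holds in two limited parts.

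The ICER is worded without baseline adjustment in a trial that expects baseline imbalance and adjusts for it elsewhere. A one-standard-error imbalance of 0.03 would move the QALY difference by 0.009 to 0.012, about 25 to 41% of the gain implied by the planned effect. A reader might infer that it could equal the whole effect. That is so only against a much smaller effect: a utility gain of 0.03 at both follow-ups yields 0.03 × 0.375 = 0.011 QALY. The article does not plan for an effect of that size. The error is one of chance in the realised trial and has no fixed sign.

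Programme delivery cost is not named in either component of societal cost. Leaving it out would understate incremental cost by about 2 to 4 staff hours, or EUR 80 to 330, per intervention dyad. This part does have a clear direction, but the net direction for the ICER as a whole is not determined.

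The sizes rest on the trapezoid rule and on assumed utility SD, slope, ICC, centre size, visit length and hourly rate, none of which the article gives. The structural points do not depend on the particular values.

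**What to change.** 1. State that incremental QALYs are estimated from a model adjusted for baseline EQ-5D utility, and incremental DQOL from one adjusted for baseline DQOL. Both models should account for the centre clusters, and both should be fitted within each bootstrap replication.
2. State that total societal cost includes programme delivery (sessions, home visits, trainer training, manuals), the productivity and medication costs already valued under Cost analysis, and residential care within the 6-month horizon.

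The cost is small. Baseline EQ-5D and DQOL are already collected, and session attendance is already recorded. Delivery cost needs only logs of session and home-visit time. The analysis becomes slightly more involved, and the ICER may come out less favourable.

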## Discussion

Because of the expected increase in the number of people with dementia worldwide, there is an urgent need to develop, evaluate and effectively implement evidence-based psychosocial interventions to support informal caregivers of people with dementia. If the caregiver feels better equipped to care for the person with dementia, a better quality of life can be maintained by both the caregiver and the person with dementia, and placement in a nursing home can be delayed. This paper describes the study protocol of a randomised controlled trial of the MOMANT caregiver support program for caregivers of home-dwelling people with dementia. This intervention, which combines multiple proven effective support components and pays much attention to its implementation, gives caregivers the tools and techniques to better care for their relative with dementia, but also engages the person with dementia through participation in stimulating activities. In addition to the RCT, a process evaluation is carried out to identify possible facilitators and barriers to implementation of the intervention as well as intervention fidelity, which may potentially influence its effectiveness. We anticipate that all data collection will be completed by December 2021.

A major strength of the current study is that the MOMANT program will take place at local health care organizations in such a way that staff costs and demand on health care services are reduced by training the informal caregiver to provide part of the intervention, and by working with an implementation manual. If study outcomes confirm the effectiveness of the implementation of this intervention, the MOMANT caregiver support program can be further implemented in real-world practices and routine care pathways, thus increasing the number of effectively supported informal caregivers. A second strength of this study is that the intervention includes activities for the caregivers and persons with dementia to do together in order for the person with dementia to be able to participate again in day-to-day life. Additionally, the fact that participants are included across different parts of the Netherlands ensures diversity in the group such that contextual differences can also be assessed. However, letting informal caregivers present part of the intervention could also be considered a limitation in terms of intervention fidelity, resulting in less visibility in the actual practice of how the intervention is presented. Moreover, because of the cluster randomisation there could be a risk of between-group differences at baseline, as well as only recruiting people with dementia who already receive professional (day)care. Despite these limitations, evaluating the effectiveness of this intervention will be a starting point in offering more support to this group of people in the routine care pathways, and therefore also be beneficial for those who do not yet receive professional care.

Effective psychosocial interventions for community-dwelling people with dementia and their caregivers are of the utmost relevance because the number of people suffering from dementia will continue to rise in the years to come, and the large majority lives and are cared for at home by informal caregivers. This study will not only contribute to the knowledge on the effectiveness of a multicomponent training and support intervention, but also on its implementation in regular care. Through this intervention, we hope to empower both the caregiver and the person with dementia to live a good life with dementia and to become more capable in dealing with future challenges.

## Data Availability

All research data will be archived and securely stored for 10 years after the end point of the study. The datasets generated during and/or analysed during the current study are available from the corresponding author on reasonable request.

## Abbreviations

CES-D1: Center for Epidemiologic Studies – Depression
DQOL: Dementia Quality of Life
GDS: Global Deterioration Scale
ICERS: Incremental cost-effectiveness ratios
IDDD: Interview for Deterioration in Daily Living Activities in Dementia
PES: Positive Experiences Scale
PES-AD: Pleasant Events Schedule-Alzheimer’s Disease
PRODISQ: Productivity and Disease Questionnaire
QALY: Quality-adjusted life-years
RCT: Randomized controlled trial
RUD: Resource Utilization in Dementia
SSCQ: Short Sense of Competence Questionnaire
VAS: Visual Analogue Scale
VU: Vrije Universiteit
WHO: World Health Organisation
